#### Analysis 1 secondary analyses

Exploratory analyses will be conducted to elucidate possible effect modification by the baseline variables on the efficacy of each component and of the proposed optimum combination(s) of components. The psychometric characteristics of the baseline questionnaires (internal consistency reliability, factor validity, and construct validity) will be ascertained. The ordering effect between BA and CR will be examined through comparison of the eight combinations in which CR comes before BA and the eight combinations in which BA comes before CR. The expected total sample size for this comparison is 272 (17 × 8 × 2). The comparison will have 70% power to detect an effect size of 0.3 at alpha = 0.05. Further exploratory analyses will be conducted on the mediator variables and use statistics of the smartphone CBT to examine the process of the therapy. Where repeated-measures analysis is not possible (e.g., cognitive behavioral skills), we will use multiple imputation for missing observations, where appropriate. The enduring effects of the 2-month intervention among those with elevated distress at baseline will be examined at week 52.

#### Analysis 2 main analyses at week 52

The primary outcome for analysis 2 is the incidence of a MDE by week 52 among all participants with or without elevated distress at baseline but without baseline MDE. We will use the mixed-effects logistic regression analysis to estimate the OR for each component. The model will include random effects for subjects (as intercepts) and fixed effects of treatment (main effects and second-order interaction effects of the five components), visit (as categorical) and treatment-by-visit interaction, university, age, sex, and baseline PHQ-9 scores.

An exploratory analysis will be conducted to compare the incidence of MDE between the proposed optimum combination(s) with the other combinations, which do not contain such components, through the time-to-event analysis (Kaplan-Meier survival analysis) among those who did not have an MDE at baseline. The influence of baseline characteristics on the time to event will be explored by use of Cox proportional hazards analysis if the proportional hazards assumption is met. This analysis is only exploratory, rather than confirmatory, because the efficacy of the proposed optimum combination(s) will be confounded by the correlations of depression scores and status between the 9-week outcomes, from which the proposed combination(s) are derived, and the 52-week outcomes, which are correlated with the outcome of this analysis.

Even when we include all participants with all baseline PHQ-9 scores, the power for analysis 2 may be low owing to the low event rates among the participants. The post hoc power calculation will be conducted for the expected 50% reduction in terms of OR or HR.

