### Measurements

#### Primary outcomes

The primary outcome of analysis 1 is self-administered PHQ-9 at week 8. The primary outcome of analysis 2 is incidence of a MDE as assessed by the MDE section of the computerized CIDI at week 52.

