#### Background characteristics

The following background characteristics will be measured at baseline:DemographicsAgeSexCourse (doctoral/master/undergraduate) and class (1/2/3/4: if repeated or not)MajorMarital statusDomicile (home/lodging)Part-time employment (no/less than 2 h per week/2–10 h/more than 10 h)Involvement in club activities (no/less than 2 h per week/2–10 h/more than 10 h)History of psychological/psychiatric treatmentSmoking (none/10 cigarettes/20 cigarettes/30 or more cigarettes per day)Drinking (none/less than 2 units per day/2 or more units per day/problem drinking)Exercise (rarely/sometimes/daily)Breakfast (rarely/sometimes/every day)PersonalityShort form of the Big Five scale (29 items) [37, 38]Short form of the Autism Spectrum Quotient (ten items) [39]Social supportSocial Support Questionnaire (12 items) [40, 41]Cognitive and behavioral skillsSelf-monitoring (five items) [30]Cognitive restructuring (six items) [31]Behavioral activation: Behavioral Activation for Depression Scale-Short Form (eight items) [32, 33]Assertiveness (seven items) [34]Problem solving (six items) [35]Clinical characteristicsPHQ-9 [28]GAD-7 [42]Major depression section of the computerized World Health Organization (WHO) CIDI [43, 44]FunctionPresenteeism scale from the HPQ [36]

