#### CIDI

We will use the self-administered version of the Japanese WHO-CIDI 3.0 depression section [49, 50] to ascertain the diagnosis of a major depressive disorder according to DSM-IV in the past 12 months. The self-administered version has been shown to have good concordance with the clinical diagnosis of MDE [51] and to be reliable in a 1-year test–retest survey [44].

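### Analysis 2 primary model carries repeated-measures terms (subject intercept, visit, treatment-by-visit) for an MDE outcome that the text measures only once after baseline

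*Protocol article*

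**What the plan says.** Under Primary outcomes, the analysis 2 endpoint is "incidence of a MDE as assessed by the MDE section of the computerized CIDI at week 52". The CIDI section says the self-administered depression section is used "to ascertain the diagnosis of a major depressive disorder according to DSM-IV in the past 12 months", so one interview at week 52 looks back over the whole follow-up. The only other administration named in the text is at baseline, where Background characteristics lists "Major depression section of the computerized World Health Organization (WHO) CIDI". Secondary outcomes gives visit weeks for PHQ-9, GAD-7, the skills scales and the presenteeism scale, and names no further CIDI.

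Under Analysis 2 main analyses at week 52, the population is "among all participants with or without elevated distress at baseline but without baseline MDE". The model follows: "We will use the mixed-effects logistic regression analysis to estimate the OR for each component". Its terms are then listed: "The model will include random effects for subjects (as intercepts) and fixed effects of treatment" (main effects and two-way interactions of the five components), then "visit (as categorical) and treatment-by-visit interaction, university, age, sex, and baseline PHQ-9 scores".

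The same set of terms appears under Analysis 1 main analyses at week 8, for the PHQ-9.

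**The concern.** A subject random intercept describes correlation among repeated values from one person. A visit factor and its interaction with treatment describe how effects differ between occasions. All three suit the PHQ-9, which is collected weekly to week 8 and every four weeks afterwards. They need at least two informative outcomes per person, and the text gives the MDE endpoint only one.

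At stake is the reported odds ratio per component, which is the stated aim of the analysis. If the model is run as written, the analyst will meet aliased terms and a variance that the data barely inform. The choice of what to drop or hold fixed would then be made after the data are in, and could differ between software packages.

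**Working it through.** The plan gives no figure for this model, so there is none to reproduce. The check concerns identifiability.

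**1. Informative outcomes per participant**

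| Occasion | Where stated | MDE value among those analysed |
|---|---|---|
| Baseline | Background characteristics | 0 for everyone, because a baseline MDE excludes |
| Between baseline and week 52 | no CIDI named in Secondary outcomes | none |
| Week 52 | Primary outcomes | 0 or 1 |

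One informative binary value per person.

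**2. Fixed effects with one visit**

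Intercept 1 + main effects 5 + two-way interactions 10 + age, sex and baseline PHQ-9 3 = 19 columns. Visit adds 1 and treatment-by-visit adds 15, so 19 + 16 = 35. With a single visit, the visit column is constant and equals the intercept. Each treatment-by-visit column is a treatment column multiplied by 1. The computed rank is 19, so 16 columns are redundant. University was left out; adding it does not remove the redundancy.

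**3. Baseline counted as a second visit**

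Every baseline value is 0 by the entry rule, so the fitted baseline log-odds run to minus infinity. The likelihood contribution of those rows then tends to 1 whatever the random intercept or treatment. They carry no information on either, and step 4 still applies.

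**4. Random-intercept variance with one binary value per person**

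The likelihood uses p_i = ∫ expit(x_i′β + σu) φ(u) du. With one value per person there is no within-person correlation to estimate. σ enters only through the shape of the curve linking x_i′β to p_i, and a larger σ can be almost offset by stretching β.

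Inputs: N = 1088 (17 × 64, the analysis 1 target, borrowed as an assumption). The protocol calls event rates low without giving a figure, so incidences of 5%, 10% and 20% were assumed. One component had an assumed true OR of 0.6, and the data were generated with no random intercept. There was one simulated dataset per rate, so the ORs at SD 0 include sampling error. The model was maximised at fixed SDs with 60-point Gauss-Hermite quadrature. Components are coded ±1, so OR = exp(2b).

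| SD | 5% (66 events): log-lik; OR; z | 10% (118 events): log-lik; OR; z | 20% (225 events): log-lik; OR; z |
|---|---|---|---|
| 0 | −227.048; 0.707; −1.23 | −342.013; 0.383; −4.25 | −510.421; 0.563; −3.57 |
| 1 | −227.264; 0.693; −1.20 | −341.777; 0.347; −4.29 | −510.206; 0.514; −3.59 |
| 3 | −227.553; 0.573; −1.18 | −341.486; 0.178; −4.34 | −509.918; 0.315; −3.63 |
| 5 | −227.587; 0.435; −1.17 | −341.447; 0.073; −4.35 | −509.878; 0.172; −3.64 |

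Change in log-likelihood from SD 0 to 5: 227.587 − 227.048 = 0.539; 342.013 − 341.447 = 0.566; 510.421 − 509.878 = 0.543. The largest doubles to 2 × 0.566 = 1.13, well below the 3.84 needed to separate two values of one parameter at the 5% level. Although no random intercept was simulated, the likelihood was highest at SD 0 in the first dataset and at SD 5, the largest tried, in the other two.

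A separate simulation with continuous covariates behaved the same way: log-likelihood −347.84 to −347.60 and OR 0.76 to 0.50 for SD 0 to 5, with z near −1.3 throughout.

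**5. After removing the three terms**

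This is the SD = 0 row: ordinary logistic regression with 19 columns, rank 19 and one OR per component.

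**The case against.** Much can be said for the plan. First, the direction and Wald test of each component barely depend on the variance, as the z columns show. Software that sets the variance to zero and drops aliased terms would return exactly the ordinary logistic OR. A reader might infer that the component ORs are arbitrary; that goes too far. Only their size is unsettled, and at an SD of 1 the drift is modest.

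Second, the likelihood is not exactly flat. It is flat when a single binary factor is the only predictor. With age and baseline PHQ-9 in the model it is nearly flat, so the fair description is practical non-identification.

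Third, the assessment schedule is in Figs. 2 and 3, which were not available for this review. If they show intermediate CIDI visits, the model could be estimable. This stands as a caveat, although Primary outcomes names week 52 alone.

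Fourth, a reader might infer that participants without a week-52 CIDI are lost unnoticed. The text does not establish that. Analysis 1 secondary analyses already plans multiple imputation where repeated-measures analysis is not possible. That sentence does not bind analysis 2, but it shows the intended approach, and further detail may be in an analysis plan that is not at hand.

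Fifth, a reader might extend the point to the exploratory comparison "through the time-to-event analysis (Kaplan-Meier survival analysis) among those who did not have an MDE at baseline" and its Cox model. The documents do not support this: time-to-event methods need onset dates, and the article does not say whether these are recorded.

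**Conclusion.** The analysis 2 primary model is wrong as written. Its visit and treatment-by-visit terms are aliased, and its random-intercept variance is practically unidentified, because the text provides one informative binary outcome per participant. The consequence is limited: the size of the component OR follows the variance the software settles on, while direction and test hardly change. Over SD 0 to 5 the drift in the simulated datasets was from 0.71 to 0.44, from 0.38 to 0.07 and from 0.56 to 0.17. Those sizes rest on the assumed N, incidences and true OR. The aliasing rests only on the CIDI schedule in the text.

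This should be fixed, but it does not threaten the trial's main result. Sample size powers the study for analysis 1, component selection rests on the week-8 analyses, the Discussion lists MDE prevention among the secondary objectives, and the analysis 2 section itself concedes that power may be low.

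**What to change.** In Analysis 2 main analyses at week 52, specify ordinary logistic regression with one row per participant: the five component main effects, their ten two-way interactions, university, age, sex and baseline PHQ-9. Delete the subject random intercept, visit and treatment-by-visit terms.

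State that the multiple imputation already planned where repeated-measures analysis is not possible also covers missing week-52 CIDI status, with the follow-up PHQ-9 scores already collected as predictors.

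If Figs. 2 and 3 contain further CIDI visits, the alternative is to define the repeated binary outcome and its visits in the text, and to state at which visit the component OR is read.

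The cost is a change of wording and simpler code, with no new data. It should be made before the week-52 data are analysed, so that the primary model is not chosen in response to a fitting problem.

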#### Interim analysis

No interim analysis is planned.

### Monitoring

#### Data monitoring

Data integrity will be monitored centrally, first through the built-in data check system on the server program and second by the data management team on a daily basis. The data management team will prepare the annual summary (number of participants entering the study, number of participants completing the study, and serious adverse events) to be presented to the data and safety monitoring board (DSMB) at 12 months, 24 months, and 36 months after the enrollment of the first participant. The DSMB will advise the steering committee as to the appropriateness of the study progress.

#### Harms

If elevated suicidal score is noted (total PHQ-9 score of 10 or more and “half or more of the time” or “almost daily” on item 9 of PHQ-9), the encouragement email will contain advice to seek help at the student health center and see a psychiatrist from the clinical management team who will judge whether any emergency intervention is necessary and whether the participation in the trial can be continued (participation itself can be continued after emergency intervention). All serious adverse events (defined as all deaths, life-threatening events, hospitalizations, enduring or conspicuous disabilities), whether they are related to the trial participation or not, will be handled according to the procedures set out by Kyoto University Hospital.

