##### Eligibility criteria for study personnel

Encouragement emails will be handled by personnel qualified in health care, such as physicians, nurses, and clinical psychologists.

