**Fig. 1 Fig1:**
[figure not shown]
Screenshots from the cognitive behavioral therapy smartphone app

Each component will consist of a lesson that is supposed to take 1 week to complete. The participants can move to the next lesson only after 1 week has passed and after they have completed one worksheet. We have demonstrated the efficacy of a smartphone CBT package containing the SM, BA, and CR components among patients with antidepressant-resistant depression in an RCT [18]. This study found that it took the participants, on average, 10.8 (SD, 4.2) days to complete one lesson; because the maximum number of components or lessons that participants undertake after PE is five, we set the length of the intervention phase of the trial to 8 weeks.

PE constitutes the core of the intervention, and all participants will receive this component. After completing PE, the participants will be randomly allocated to one of the combinations on the basis of presence/absence of the remaining five components (Table 1). In order to enable examination of the ordering effects between CR and BA, we doubled the number of combinations to 2^5^ × 2 = 64. AT and PS are placed before or after SM or CR or BA in equal proportions among these 64 combinations in order to counterbalance the anticipated likelihood that fewer participants will complete later parts of the intervention. All participants have full access to treatment as usual, inside and outside the campus.

**Table 1 Tab1:** Combinations of cognitive and behavioral components of cognitive behavioral therapy smartphone app

	PE	SM	CR	BA	AT	PS	Sequence of administration								No.
C1	1	1	1	1	1	1	PE	AT	PS	SM	CR	BA			17
C2	1	1	1	1	1	1	PE			SM	BA	CR	AT	PS	17
C3	1	1	1	1	1	−1	PE			SM	CR	BA	AT		17
C4	1	1	1	1	1	−1	PE	AT		SM	BA	CR			17
C5	1	1	1	1	−1	1	PE		PS	SM	CR	BA			17
C6	1	1	1	1	−1	1	PE			SM	BA	CR		PS	17
C7	1	1	1	1	−1	−1	PE			SM	CR	BA			17
C8	1	1	1	1	−1	−1	PE			SM	BA	CR			17
C9	1	1	1	−1	1	1	PE			SM	CR		AT	PS	17
C10	1	1	1	−1	1	1	PE	AT	PS	SM	CR				17
C11	1	1	1	−1	1	−1	PE			SM	CR		AT		17
C12	1	1	1	−1	1	−1	PE	AT		SM	CR				17
C13	1	1	1	−1	−1	1	PE			SM	CR			PS	17
C14	1	1	1	−1	−1	1	PE		PS	SM	CR				17
C15	1	1	1	−1	−1	−1	PE			SM	CR				17
C16	1	1	1	−1	−1	−1	PE			SM	CR				17
C17	1	1	−1	1	1	1	PE			SM		BA	AT	PS	17
C18	1	1	−1	1	1	1	PE	AT	PS	SM		BA			17
C19	1	1	−1	1	1	−1	PE			SM		BA	AT		17
C20	1	1	−1	1	1	−1	PE	AT		SM		BA			17
C21	1	1	−1	1	−1	1	PE			SM		BA		PS	17
C22	1	1	−1	1	−1	1	PE		PS	SM		BA			17
C23	1	1	−1	1	−1	−1	PE			SM		BA			17

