### Strategies to improve adherence to interventions and procedures for monitoring adherence

The participants will receive a semiautomated email to congratulate them for their progress in the program every week. The message is based on a template focusing on adherence and motivation but can be modified by a physician or a clinical psychologist on the study team. It can contain technical advice for the program, but the participant will be referred to the student health center for any psychological advice.

The adherence of the participants to the allocated intervention will be uploaded and recorded by the online server program. The study personnel will have access to the server and perform ongoing monitoring of adherence of the participants.

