#### Secondary outcomes

The secondary outcomes are as follows:PHQ-9 at weeks 1, 2, 3, 4, 5, 6, 7, 12, 16, 20, 24, 28, 32, 36, 40, 44, 48, and 52Generalized Anxiety Disorder-7 (GAD-7) at weeks 4, 8, and 52Cognitive and behavioral skills [30–35] at weeks 8 and 52Presenteeism scale from the Health and Work Performance Questionnaire (HPQ) [36] at weeks 8 and 52Use statistics of the smartphone app through the trialCointerventions (visits to a mental health professional, psychotropics, counseling/psychotherapy)

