### Measures

#### Personal Health Questionnaire-9 (PHQ-9)

PHQ-9 consists of the nine diagnostic criteria items for a MDE in the *Diagnostic and Statistical Manual of Mental Disorders, Fourth Edition* (DSM-IV), and the DSM-5 [28]. Each item is rated from 0 = *Not at all* through 3 = *Nearly every day*, with the total score ranging therefore between 0 and 27. The reliability and the validity of the original PHQ-9 and its Japanese version are well established [45, 46]. We used this scale successfully in our previous trial of the smartphone CBT [18].

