#### Plans to promote participant retention and complete follow-up

The outcome data will be collected even when the participant has not completed the allocated intervention, unless he/she has expressed a wish to completely withdraw from the study. When the participant fails to fill in the scheduled assessments, reminders will be sent in 24 hours and 48 hours via automated popup on the smartphone. If the participant still has not filled in the assessment, a semiautomated email will be sent once as a gentle reminder. No further attempt will be made for that assessment. The participants will receive modest compensation for the time it requires to fill in the questionnaires: 1000 yen when they complete week 4 assessment, 2000 yen when they complete week 8 assessment, and 2000 yen when they complete week 52 assessment.

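### The in-trial suicidality response requires a PHQ-9 total of 10 or more, so a high item 9 answer at a total of 9 or less triggers no targeted response

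*Protocol article*

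**What the plan says.** The rule is in the Harms section under Monitoring. It starts "If elevated suicidal score is noted (total PHQ-9 score of 10 or more and" and continues with the two most frequent answer categories of item 9. When it is met, the encouragement email advises the participant to seek help at the student health center and to see a psychiatrist from the clinical management team. That psychiatrist decides whether emergency intervention is needed and whether participation can continue.

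Other parts of the protocol article that bear on the rule:

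- Exclusion criteria: a PHQ-9 of 10 or more at screening is an exclusion. No criterion refers to item 9.
- Measures, PHQ-9: nine items are each rated 0 to 3, "with the total score ranging therefore between 0 and 27".
- Secondary outcomes: "PHQ-9 at weeks 1, 2, 3, 4, 5, 6, 7, 12, 16, 20, 24, 28, 32, 36, 40, 44, 48" and week 52.
- Primary outcomes: "The primary outcome of analysis 1 is self-administered PHQ-9 at week 8".
- Eligibility criteria for study personnel: "Encouragement emails will be handled by personnel qualified in health care".
- Strategies to improve adherence: "The participants will receive a semiautomated email to congratulate them for their progress in the program every week". The text comes from a template about adherence and motivation, which a physician or clinical psychologist can modify.

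**The concern.** Item 9 is the item that the rule itself uses to identify suicidality. By adding a condition on the total, the rule makes the response to frequent suicidal thoughts depend on how many other depressive symptoms are reported. The population has been selected to have few of them: every participant screened at 9 or less, and the rule starts at 10. A student who reports such thoughts on half or more of the days, with few other symptoms, falls outside it.

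The issue is participant safety. No estimate, test or sample size is affected. The article states the rule outright, so this is not a detail left to a fuller document. The point covers PHQ-9 assessments completed by enrolled participants. The article does not describe how a high item 9 answer is handled at screening, and that is not part of the point.

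**Working it through.** **Inputs.** The trigger is a total of at least 10 together with item 9 at one of its top two answers (Harms). Items run from 0 to 3 (Measures, PHQ-9). The screening total is at most 9 (Exclusion criteria). Assumption: the top two answers score 2 and 3, which follows from the 0 to 3 scale although the article does not print the score next to each label.

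**Uncovered combinations.** Total = item 9 + sum of the other eight items.

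- Item 9 = 2: the smallest total is 2. The rule does not apply at totals 2 to 9, which is 9 − 2 + 1 = 8 totals. To reach 10, the other eight items must sum to at least 10 − 2 = 8.
- Item 9 = 3: the smallest total is 3. The rule does not apply at totals 3 to 9, which is 9 − 3 + 1 = 7 totals. To reach 10, the other eight items must sum to at least 10 − 3 = 7.
- Together: 8 + 7 = 15 combinations of item 9 answer and total. Example: item 9 = 3 with 6 points on the other items gives 3 + 6 = 9, and no trigger.

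**What a new high answer does for someone who is otherwise stable.** Take a participant who screened at T with item 9 = 0 and whose other eight answers stay the same.

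- Moving to item 9 = 2 gives T + 2, which reaches 10 only if T ≥ 8.
- Moving to item 9 = 3 gives T + 3, which reaches 10 only if T ≥ 7.

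So for screening totals of 0 to 6, neither answer triggers the rule unless other symptoms also worsen. At T = 7 only the top answer triggers it. At T = 8 or 9 both do.

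**Number of occasions.** Weeks 1 to 7 give 7 assessments, week 8 gives 1, and weeks 12, 16, 20, 24, 28, 32, 36, 40, 44, 48 and 52 give 11. The total is 7 + 1 + 11 = 19.

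**Do other provisions close the gap?** Each was checked for a link to item 9:

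- Interventions: psychoeducation, which everyone receives, includes information on campus resources. It is given once, before randomization, whatever the answers.
- Study personnel and adherence sections: qualified staff handle the emails and a clinician may modify them. This allows action below the threshold but does not require it.
- Criteria for discontinuing: the steering committee may stop an intervention. No suicidality criterion is given.
- Anticipated risks and benefits: close monitoring is mentioned directly after a sentence on serious adverse events, with no item 9 threshold.
- Concomitant care and posttrial care: usual care is open to all. The Background section notes that only a minority of distressed students seek professional help.
- Data monitoring: the annual summary for the monitoring board covers enrolment, completion and serious adverse events.

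None of these is set off by an item 9 answer.

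**Wording.** The natural reading is total ≥ 10 and (item 9 = 2 or item 9 = 3). A strained reading is (total ≥ 10 and item 9 = 2) or item 9 = 3. Under the strained reading the 7 combinations with item 9 = 3 are covered, and the 8 combinations with item 9 = 2 remain uncovered.

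**The case against.** The strongest reply is that this is a choice of threshold. The protocol was approved by the ethics committee, the compound rule keeps alerts fewer, and staff are free to act below it. The article condenses protocol version 1.0.1, and handling of lower scores in that unseen document cannot be ruled out. That much stands, and it keeps the point modest. It does not remove the point: the article states the compound rule explicitly, gives no reason for the total-score condition, and links nothing else to item 9.

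Four stronger conclusions are tempting but unsupported.

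- A reader might infer that psychiatrist review is guaranteed above the threshold and lost below it. The natural grammar is that the email advises the participant to see a psychiatrist, so what is secured above the threshold is targeted advice.
- A reader might infer that a participant must worsen by the full distance from the screening total to 10. Item 9 itself supplies 2 or 3 of those points, and a student who screened at 8 or 9 with item 9 = 0 can trigger the rule through item 9 alone.
- A reader might infer that 15 combinations over 19 assessments measure how many students are affected. They describe what is possible. The article gives no item 9 frequencies.
- A reader might infer that the response has no delivery route after week 8, because the weekly emails follow program progress and "we set the length of the intervention phase of the trial to 8 weeks". The article states no end date for those emails, so this is a separate, inferred question and adds no weight here.

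**Conclusion.** The point holds in limited form. As written, an enrolled participant with item 9 = 2 at a total of 2 to 9, or item 9 = 3 at a total of 3 to 9, receives no response triggered by that answer at any of the 19 post-baseline assessments. On the strained reading the gap shrinks to item 9 = 2 at totals 2 to 9, but it does not close. General provisions exist for everyone, so it would be wrong to say that such a participant is without support. What is missing is a response linked to the answer. The number of participants affected is unknown. The conclusion rests on the 0 to 3 scoring of item 9 and on the article's rule being the operative one. It is a cheap improvement to participant safety, not a contradiction or a miscalculation.

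**What to change.** Remove the total-score condition from the Harms section, so that item 9 at either of its top two answers triggers the existing response at every PHQ-9 completed by an enrolled participant, whatever the total. Reword the sentence so that it has only one reading.

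The cost is a short amendment through the route in the Protocol amendments section and a changed flag on an item that the app already collects. The downside is some additional alerts for the clinical management team; how many cannot be estimated from the article. Allocation, endpoints and sample size are untouched. Recruitment was under way when the article was submitted, so the change could still have applied to current participants.
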